**Figure 1 figure1:**
[figure not shown]
Participant timeline of activities.

### Participants

A convenience sample of 30 individuals with unilateral transfemoral limb loss will be recruited for this study (Textbox 1 shows the inclusion and exclusion criteria). All participants will consent to participate before participating in any study activities. The participants will be randomly stratified into 2 study arms: group A, a powered ankle-foot device with device-specific PT (15/30, 50%), and group B, a powered ankle-foot device with standard of practice (15/30, 50%), which includes basic device education and training but no device-specific PT intervention. Recruitment of participants will be on a first-come, first-serve basis among the patients of VANYHHS, JAHVH, and WRNMMC. The participants will be recruited through the VANYHHS, JAHVH, and WRNMMC rehabilitation and prosthetic clinics. All participants will have experience using a microprocessor knee and will currently use a passive-elastic ankle-foot prosthesis.

Inclusion and exclusion criteria.
**Inclusion criteria**
Unilateral transfemoral limb loss because of any etiologyUse of a microprocessor knee with >6 months of experience≤8 limb loss–related physical therapy sessions in the previous 6 monthsAged at least 18 yearsScore of ≥33 on the Amputee Mobility Predictor, corresponding to a high K2 or above ambulatorAble to walk a minimum of 30 meters without an assistive deviceAble to walk on a treadmill for 5 minutes at self-selected speed with or without the use of handrails
**Exclusion criteria**
Inability to tolerate the wearing of a socket or a poorly fitting socketConditions of the intact limb prohibit prosthesis use (eg, ulcers, sores, skin breakdown, burns, poor skin coverage, contractures, and severe heterotopic ossification)The length of the residual limb prohibits socket or prosthesis fittingCognitive deficits or a mental health pathology limiting the ability to participate fully in the study or any deficit deemed by the principal investigator to be detrimental to the completion of the studySignificant comorbidity, which would interfere with the study (eg, neuropathy, uncontrolled diabetes, receiving dialysis, insensate feet, severe phantom pain, or a history of skin ulcers)Severe circulatory problems, including peripheral vascular disease and pitting edemaPregnant women in the second trimester or beyond or women who will be in the second trimester within the enrollment periodWeigh >130 kg at screeningUse of nonprescribed opioids or overuse of any prescription drugsMajor upper limb lossCurrently uses a powered ankle-foot prosthesis as a primary prosthesis or used a powered ankle-foot device as a primary prosthesis in the previous 6 monthsAny cardiopulmonary, metabolic, or integumentary diagnosis where walking for 15 minutes is contraindicated

### Ethical Considerations

This study was approved by the following institutional review boards (IRBs): VANYHHS IRB (1643), WRNMMC IRB (WRNMMC-2018-0167), and the University of South Florida IRB, which is the IRB of record for JAHVH (IRB STUDY000870). The oversight and protection of human participants was also approved by the US Army Medical Research and Development Command Office of Human Research Oversight (E04081). All participants will provide informed consent before participating in any study activities.

### Baseline Visit

#### Informed Consent, Enrollment, and Randomization

Informed consent for each potential participant will be conducted in person in a private room. The site-principal investigator or qualified designee will explain the study protocol in detail. The participants will be asked to consent to randomization of the treatment group, either to be fit with the powered ankle-foot device and receive device-specific PT (group A) or to be fit with the powered ankle-foot device and receive the current standard of practice that does not include device-specific PT (group B). The participants will be asked to make a commitment to be available for all study-related activities. The individuals will be given adequate time to review and comprehend all information about the study before agreeing to participate, minimizing the possibility of coercion and undue influence. After the study has been explained and consent has been given, the participants will be randomized into the 2 groups using a computer-generated algorithm that block randomizes participants into each group at each site.

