**Methods:**

This prospective, multisite study will enroll 30 individuals with unilateral transfemoral limb loss. At baseline, participants will undergo a full gait analysis and assessment of function, neurocognition, cognitive load, subjective preferences, and pain using their current passive prosthesis. The participants will then be fitted with a powered ankle-foot device and randomized into 2 equal groups: a powered device with a device-specific rehabilitation intervention (group A) or a powered device with the current standard of practice (group B). Group A will undergo 4 weeks of device-specific rehabilitation. Group B will receive the current standard of practice, which includes basic device education but no further device-specific rehabilitation. Data collection procedures will then be repeated after 4 weeks and 8 weeks of powered ankle use.

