## Methods

### Study Overview

This investigation will be a prospective, multisite study including VA New York Harbor Healthcare System (VANYHHS), James A. Haley Veterans’ Hospital (JAHVH), and Walter Reed National Military Medical Center (WRNMMC). Enrollment began in September 2018, and data collection is expected to conclude in 2024. Briefly, 30 individuals with transfemoral limb loss are expected to be enrolled equally across the 3 sites. For all participants, a full biomechanical gait analysis, functional measures, surveys, neurocognitive assessment, cognitive load assessment, and pain assessment will be captured at baseline with their clinically prescribed passive energy storing and returning ankle-foot prosthesis. The participants will be fitted with a powered ankle-foot device (Empower) and then be evaluated for safe use. The participants will then be randomly assigned into 2 groups: a powered ankle-foot device with a 4-week, 8-session device-specific PT intervention (group A) or a powered ankle-foot device with the current standard of practice (group B), which includes basic device education and training provided by the study prosthetist (outlined in the Powered Ankle-Foot Device Standard of Practice section), but no device-specific PT intervention. Group A will then undergo 4 weeks of device-specific rehabilitation, while group B will not receive any further PT. All participants will then undergo a full gait analysis as well as assessments of function, subjective preferences, neurocognition, cognitive load, and pain after 4 weeks and 8 weeks of powered ankle-foot device use (Figure 1). A comparison between the 2 groups will help evaluate the efficacy of a powered versus passive prosthesis, as well as elucidate the contribution of device-specific effects to rehabilitation-specific effects for individuals with transfemoral limb loss.

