#### Baseline Data Capture

Regardless of the group assignment, all participants will undergo baseline data capture using their current passive energy storing and returning prosthesis. The study prosthetist will ensure proper fit and alignment of the prosthesis before any data collection. Once fit and alignment are confirmed, the participants will complete 3 surveys: an assessment of quality of life, the Prosthesis Evaluation Questionnaire (PEQ), and the PEQ Addendum. Then, pain, cognitive load, neurocognition, biomechanical gait analysis, and functional outcomes will be captured at baseline for all participants on their current passive energy storing and returning prosthesis.

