#### Powered Ankle-Foot Prosthesis Fitting

Following all baseline data collection procedures, all participants will then be fit with the Empower. Study prosthetists at VANYHHS, WRNMMC, and JAHVH are highly experienced in fitting all commercial microprocessor knees and the Empower. The study prosthetists will bench align the powered ankle-foot device onto the participant’s existing microprocessor prosthetic knee and socket. Once the powered ankle-foot device is fitted and bench-aligned to the prosthetic knee and socket, dynamic alignment of the prosthetic knee and ankle will occur. Initially, the study prosthetist will ensure proper alignment of the microprocessor prosthetic knee with the Empower turned off. The Empower will still function (ie, articulate) with the power off but will not provide net positive plantarflexion torque. The microprocessor prosthetic knee software and prosthesis alignment will be adjusted during standing and walking tasks, as necessary, until the prosthetist and the participant are satisfied with the knee alignment. Once the microprocessor knee setup is completed, the Empower will be powered on and adjusted according to the manufacturer’s specifications. Briefly, the participants will sequentially walk at 3 different speeds (slow, self-selected, and fast) while the stiffness and power delivery of the powered ankle-foot device is tuned [33]. If further dynamic adjustments to prosthetic knee alignment are necessary, these adjustments will be made at this point.

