#### Powered Ankle-Foot Device Standard of Practice

Once a stable and comfortable alignment has been established, all participants will be educated by the study prosthetist on the proper use of the Empower, which includes battery handling and charging, understanding low battery indicators, considerations while driving with the Empower (if applicable), and avoidance of exposure to rain and water. Next, the participants will ascend and descend an Americans with Disabilities Act–compliant ramp under the supervision of the study physical therapist or prosthetist. The intent of ramp walking is to trigger the power for ascent but not during descent. Each participant will be given the opportunity to practice the ramp as often as necessary to ensure safe and comfortable use. The participants will then negotiate a standard staircase with handrails under the supervision of the study physical therapist or prosthetist to ensure that they can safely negotiate stairs using the Empower. Proper technique will consist of demonstrating the correct foot placement on each step to activate powered push off during ascent. Participants unable to ascend stairs in a step-over-step pattern will be shown the correct foot placement using a step-to gait pattern. For proper stair descent, participants will be shown the correct foot placement to initiate rollover and not trigger the power. Participants will be given time to practice stair ascent and descent. After stair and ramp ambulation, participants will be asked to demonstrate safe use of the Empower in different situations, including turning, varying speeds, sudden stops, obstacle avoidance, stepping over obstacles, and different surfaces. Once the physical therapist is satisfied that the participant has demonstrated safe use and all questions have been answered, the participant will be released home with the Empower. If the physical therapist feels that the progress is unsatisfactory, the participant will not take the Empower home and will be asked to return for continued supervised use until the participant demonstrates safe use. The standard of practice to use the powered prosthesis is approximately 30 to 45 minutes after fitting and tuning.

Following the baseline visit, group A will undergo the device-specific PT program, whereas group B will not undergo any further training.

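### The article gives two incompatible positions for randomisation: after baseline testing and fitting (Abstract, Study Overview), or at the consent step, before baseline capture (Baseline Visit section)

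*Protocol article*

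**What the plan says.** The article describes the sequence of events in three places.

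- **Abstract, Methods.** After baseline assessment on the passive prosthesis: "The participants will then be fitted with a powered ankle-foot device and randomized into 2 equal groups". The safe-use check is not mentioned.
- **Study Overview.** Baseline capture on the passive prosthesis comes first. Participants are then fitted with the powered device and "evaluated for safe use. The participants will then be randomly assigned into 2 groups".
- **Baseline Visit.** The first subsection, on consent, enrolment and randomisation, says "After the study has been explained and consent has been given, the participants will be randomized into the 2 groups using a computer-generated algorithm", with blocks within site. The next subsection, Baseline Data Capture, opens with "Regardless of the group assignment, all participants will undergo baseline data capture using their current passive energy storing and returning prosthesis". The fitting subsection starts: "Following all baseline data collection procedures, all participants will then be fit with the Empower". The Standard of Practice subsection then covers education and the safe-use check, and adds: "If the physical therapist feels that the progress is unsatisfactory, the participant will not take the Empower home". Such a participant returns for further supervised use until safe use is shown.

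The power analysis section bases the sample size on the group-by-time interaction, with a baseline and two later measurements and 15 participants per group.

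**The concern.** In a two-arm comparison of change, baseline should be fixed before anyone can be influenced by the allocation. The arms differ by a visible course of physical therapy, so participants cannot be blinded once told. The simple protection is to finish baseline first. The Study Overview keeps that protection; the Baseline Visit text does not.

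Three things are at stake.

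1. **Baseline measures.** Quality of life, the Prosthesis Evaluation Questionnaire (PEQ), pain interference and the attention ratings are self-reported. The 6-minute walk and the cognitive tasks depend on effort. Two of the five measures used for the power calculation, 6-minute walk distance and PEQ utility, are of these kinds.
2. **Discretionary steps.** The study prosthetist tunes stiffness and power delivery, and the physical therapist decides when the device goes home. Under the early order both follow allocation.
3. **The randomised set.** Whether a participant who is never fitted or never cleared is a randomised participant or a pre-randomisation exclusion depends on which text governs.

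**Working it through.** The check is mainly a comparison of sequences. The article states no figure that needs reproducing on this point.

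**Order of events, side by side**

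| Source | Order |
|---|---|
| Study Overview | baseline → fitting → safe-use evaluation → randomisation |
| Abstract, Methods | baseline → fitting and randomisation (safe-use check not mentioned) |
| Baseline Visit subsections, in turn | consent → randomisation → baseline → fitting → safe-use check |

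Counting consent as step 1, randomisation is step 5 in the Study Overview and step 2 in the Baseline Visit text.

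**Can the texts be read as one order?** Taken alone, the randomisation sentence makes consent a precondition and sets no time limit. Two features of the surrounding text favour the early reading. The sentence stands ahead of Baseline Data Capture in a visit description that otherwise runs in time order, as the opening of the fitting subsection shows. The opening of Baseline Data Capture also refers to the group assignment. The Study Overview is explicit in the other direction. No single order fits the natural reading of both.

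**How a baseline shift would enter the comparison.** For a group-by-time contrast with baseline as one of the repeated measurements:

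effect = (follow-up A − baseline A) − (follow-up B − baseline B)

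If the mean baseline in group A is lowered by d for reasons linked to the allocation and follow-up is unaffected, the contrast rises by d. The same shift in group B lowers it by d. A model that adjusts for baseline as a covariate would carry only part of d, depending on the baseline slope.

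**Scale only.** The article gives no value for d. Against the 60 m planning difference in Table 5:

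- d = 5 m (assumed): 5/60 = 8%
- d = 10 m (assumed): 10/60 = 17%
- d = 20 m (assumed): 20/60 = 33%

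**Randomised set.** With 15 per group, each participant whose status is ambiguous is 1/15 = 6.7% of a group. This is the weight of one case, not an expected loss.

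**The case against.** The strongest reply is that this is loose drafting in a condensed article. The phrase about group assignment can simply mean that both arms are treated alike. The Study Overview gives an explicit sequence, and if that sequence was followed no bias of this kind arises. The full protocol may also say when the allocation is disclosed. This limits what can be claimed, but it does not remove the contradiction: the article states the order more than once, and differently.

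Three further points stand.

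- **A reader might infer that baseline tests are run with the arm already known.** The text does not say so. At most it shows that the group is already assigned; it is silent on who has been told.
- **A reader might infer that participants who fail the safe-use check are lost after randomisation.** The Standard of Practice subsection brings them back for continued supervised use and describes no withdrawal. The exclusion criteria already screen out several causes of fitting failure, and no failure rate is given.
- **Not every measure is equally exposed.** The gait measures are taken at controlled walking speeds and leave less room for effort or expectation than the surveys or the 6-minute walk. The handling of baseline in the mixed models is not detailed here, so full carry-over of a shift is not certain.

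**Conclusion.** The contradiction holds and needs correcting. As written, a reader cannot tell whether baseline precedes or follows randomisation, or when a participant enters the randomised set. Under the Baseline Visit order, baseline measures, device tuning and the release decision all follow allocation, which exposes the comparison of change to avoidable bias.

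The size of that bias is unknown. The percentages for the 6-minute walk rest on assumed shifts and on a contrast that does not adjust for baseline; they show scale and are not estimates. The documents do not support the stronger conclusions that the allocation was disclosed before baseline testing, that participants will be lost at the safe-use check, or that the trial's results are biased. Only the Study Overview puts the safe-use evaluation ahead of randomisation; the Abstract supports only the order relative to baseline and fitting.

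**What to change.** Reword the randomisation and Baseline Data Capture subsections to match the Study Overview: consent, baseline on the passive prosthesis, fitting, safe-use evaluation, then randomisation in blocks within site, with the allocation revealed only at that point. Bring the Abstract into line by naming the safe-use evaluation. State how participants who are not fitted or not cleared are counted.

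Enrolment began in September 2018 and data collection was due to end by March 2024, so the order cannot be changed for participants already enrolled. For them, report the order actually used and when the allocation was disclosed to participants and assessors. If allocation came before baseline, state this as a limitation and keep every randomised participant in the analysis set.

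The cost is a short text correction and a check of site records. One small downside for any future enrolment is that a participant who needs repeat supervised sessions would be randomised at a later visit and not on the baseline day.

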
#### Biomechanical Gait Analysis

Gait analyses will be performed at the biomechanics laboratories at VANYHHS, WRNMMC, and JAHVH. The VANYHHS laboratory is a 133-m^2^ space comprising an 11-camera motion capture system (Qualisys, Inc) with 4 multiaxis force platforms (AMTI, Inc). At WRNMMC, the biomechanics laboratory is an 167-m^2^ space comprising an 18-camera motion capture system (Qualisys, Inc) and 6 multiaxis force platforms (AMTI Inc). At JAHVH, the motion capture laboratory is a 74-m^2^ space equipped with a 12-camera motion capture system (Vicon Inc) and 4 multiaxis force platforms (AMTI Inc). All 3 systems track the positions of passive reflective markers at a rate of 120 Hz, and force platforms sample ground reaction forces at a rate of 1200 Hz. Visual3D software (C-Motion Inc) will be used for the analysis of 3D motion capture data.

All laboratories in this investigation will follow recommendations provided by an interlab reliability study that was conducted between gait laboratories at the 3 military treatment facilities [52]. Specifically, all sites will use identical marker sets, identical anatomical segment definitions, and a single examiner at each site to conduct postprocessing of the respective data to reduce potential variability between the laboratories.

For all participants, biomechanical gait analysis will be performed at baseline using their prescribed energy storing and returning prostheses. All kinematic and kinetic biomechanical measures will be captured using an identical 6-degrees-of-freedom marker set. A custom, full-body passive reflective marker set will be placed on each participant, which tracks each segment independently, allowing for the accurate measurement of movements. As previously described [53], 78 markers will be placed or digitized on the head, trunk, pelvis, and extremities. Marker placements for the prosthetic limb will be matched to those of the intact leg or placed on the centers of rotation of the prosthetic ankle-foot and knee devices. The cluster technique will be used to minimize the surface-to-bone displacements for the thigh, shank, and upper arm–mounted markers [54]. Tracking clusters will be placed bilaterally on the thigh, the tibial crest, and the upper arm. Functional joints, adapted from Schwartz and Rozumalski [55], will also be calculated for the intact ankle and knee as well as bilaterally for the hips.

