### Planned Statistical Analysis for Cognitive Load and Neurocognitive Outcomes

Linear mixed-effects models will be performed to examine the differences between the ankle-foot devices on cognitive performance, walking speed, and subjective responses to attention. The parameters in the linear effects model will include prosthetic ankle-foot type, PT intervention, and participants. Ankle-foot type, PT intervention, and cognitive performance will be treated as fixed effects, whereas participants will be treated as random. The total number of errors and the error rates for the cognitive task will be calculated, and the mean error rate will be determined for each cognitive task performed by each participant. Repeated-measures ANOVA will be used to compare the error rates for the 3 cognitive tasks. Fisher least significant difference test will be used to make post hoc comparisons.

For the neurocognitive battery, Pearson correlation coefficients (pair-wise 2-tailed) will be calculated for all variables of interest. Stepwise multiple regression will be performed with the neurocognitive scores (Neurocognitive Index, composite memory, cognitive flexibility, and complex attention scores) as the dependent variable. The independent variables will comprise functional outcomes, pain, and gait biomechanics, including asymmetry index.

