### Limitations

This investigation will not address the varied dosing, timing, frequency, and duration of the device-specific rehabilitation protocol. However, the frequency of PT visits and protocol timing will be evaluated for each participant, which can provide preliminary data for a future study to optimize the rehabilitation strategy. The heterogeneity of the sample population may also limit the generalizability of the outcomes to a more diverse population. In addition, the statistical analysis models will also adjust for specific parameters (eg, age, time since limb loss, and etiology of limb loss), which may limit the sample size and interpretability of the results. The type of microprocessor knee used by each participant will not be prescribed and may be a confounding factor. This influence of the microprocessor knee type will be evaluated in the statistical models. Finally, a 4-week assessment following completion of the device-specific protocol may not be sufficient to evaluate any PT rebound effects or long-term changes in gait, specifically regarding the effectiveness of the acute PT intervention on gait biomechanics.

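### Site is the randomisation stratum but is not named in any described model, which costs some precision in between-participant comparisons though not in the powered contrast

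*Protocol article*

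**What the plan says.** Under Informed Consent, Enrollment, and Randomization, the article says that the algorithm "block randomizes participants into each group at each site". The Study Overview says that "30 individuals with transfemoral limb loss are expected to be enrolled equally across the 3 sites", so about 10 per site, or 5 per arm per site if the blocks fill evenly.

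Under Biomechanical Gait Analysis, "Gait analyses will be performed at the biomechanics laboratories at VANYHHS, WRNMMC, and JAHVH". Two laboratories use one make of camera system and the third uses another, with different camera counts. The same section plans "a single examiner at each site to conduct postprocessing of the respective data to reduce potential variability between the laboratories" and says that "all sites will use identical marker sets, identical anatomical segment definitions" will be used. It therefore treats the laboratory as a source of variation to be controlled. The fitting section places study prosthetists at each site.

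The analysis sections describe the models. For biomechanics, the fixed effect is ankle type, with participant and participant-by-condition random effects. For cognitive outcomes, "The parameters in the linear effects model will include prosthetic ankle-foot type, PT intervention, and participants", with participants random. The general Statistical Analysis section mentions control variables without listing them. Limitations says that the models will "adjust for specific parameters (eg, age, time since limb loss, and etiology of limb loss", and adds knee type. Site is named in none of these places.

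**The concern.** Blocking within site balances the arms on whatever differs between sites. If the analysis then ignores site, the group difference is still estimated without bias, but any between-site variation in the analysed quantity is counted as residual error. The standard error is then larger than the design warrants, and the test rejects too rarely under the null and under the alternative. With 30 participants there is little precision to give away. The article names several adjusters, including one that it regards as a possible confounder (knee type), but not the one factor built into the randomisation.

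**Working it through.** **1. Where site cancels.** Write an outcome for participant i at site s and visit k as

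Y = site(s) + participant(i) + visit(k) + group-by-visit + error.

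The article does not describe participants moving between sites, so I assume that each stays at one. In a change from baseline, site(s) and participant(i) both drop out. The same holds for powered versus passive, since every participant is measured on both devices. A site-by-visit term, if there is one, does not drop out.

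**2. Simulated check.** 3 sites of 10, 5 per arm at each; between-participant variance 1 (including site), residual variance 0.5 per visit, true effect 1, two-sided 5%, 4,000 runs (Monte Carlo error about 0.007). All variances are assumptions.

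| Contrast | Site share of between-participant variance | Power without site | Power with site | Type I error without site |
|---|---|---|---|---|
| Change from baseline | 0% | 0.757 | 0.756 | 0.044 |
| | 10% | 0.742 | 0.740 | 0.052 |
| | 30% | 0.752 | 0.749 | 0.055 |
| | 50% | 0.755 | 0.754 | 0.048 |
| Groups at one follow-up visit | 0% | 0.589 | 0.590 | 0.052 |
| | 10% | 0.587 | 0.600 | 0.048 |
| | 30% | 0.611 | 0.672 | 0.036 |
| | 50% | 0.642 | 0.748 | 0.027 |
| Change, plus site-by-visit variance 0.1 | 30% | 0.725 | 0.748 | 0.041 |
| Change, plus site-by-visit variance 0.3 | 30% | 0.674 | 0.746 | 0.033 |

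A constant site effect costs nothing in the change contrast. It costs power in the single-visit comparison, and a site-specific change costs power in the change contrast.

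**3. Size for a simple between-group comparison.** Inputs are the Table 5 difference and SD with 15 per arm, two-sided 5%. The site share R of the variance is an assumption, because the article gives none.

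- Standardised difference d = difference / SD. 6-minute walk test: 60/61 = 0.984. Leading limb work: 0.03/0.04 = 0.75.
- Without site, R = 0: noncentrality = d / √(2/15), 28 df. 6-minute walk: 2.694, power 73.9%. Leading limb work: 2.054, power 50.9%.
- With site: noncentrality = d / [√(1−R) × √(2/15)], 26 df (30 − 3 − 1).

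| Measure | R | Noncentrality | Power with site | Power without site |
|---|---|---|---|---|
| 6-minute walk | 0 | 2.694 | 73.7% | 73.9% |
| | 10% | 2.839 | 78.0% | about 75% |
| | 20% | 3.012 | 82.6% | about 76% |
| Leading limb work | 0 | 2.054 | 50.7% | 50.9% |
| | 10% | 2.165 | 55.0% | about 50% |
| | 20% | 2.296 | 59.9% | about 50% |

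By simulation with site effects held at the assumed share, type I error without site is about 4.0% at R = 10% and 2.9% at R = 20%. If site explains nothing, including it costs 73.9 − 73.7 = 0.2 points.

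These are not the powers in Table 5. Across its five rows the two-sample calculation gives 51, 31, 68, 74 and 71, against the stated 85, 82, 98, 96 and 96. Table 5 refers to a group-by-time interaction over three visits, and the within-participant correlations that it needs are not given. The difference does not show Table 5 to be wrong, and it has no bearing on site.

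**4. Which planned analyses are affected.**

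- The PT term in the cognitive model, if PT is coded as the randomised arm. Its main effect is then between participants. If PT is coded as an exposure that starts after baseline, much of the contrast is within participants.
- Any comparison of the two groups at a single visit.
- The Spearman and Pearson correlations and the penalised and stepwise regressions, which have no stated participant or site term and pool the sites. The direction of the effect there cannot be derived from the article.
- The group-by-time contrast, only if sites differ in how much participants change.

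**The case against.** The strongest reply is that the main contrasts are within-participant. The mixed models carry participant random effects, and the sample size rests on the group-by-time interaction. A constant camera, examiner or site shift cancels there, and a site main effect would add nothing. This is correct. A reader might infer that between-site variance inflates the error throughout the plan, or that the trial's stated power is overstated for this reason. The documents do not support either reading.

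Second, the list of adjusters is introduced as examples and the control variables are left open, so a full analysis plan may include site. This also stands: the article does not exclude site. But the cognitive section does list its model terms, and the list omits the stratification factor.

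Third, the laboratories are harmonised: identical markers and segment definitions, the same sampling rates, the same make of force platform and the same analysis software. This should reduce site variance, though by an amount that the article does not give. The 6-minute walk, used above for size, depends on neither motion capture nor post-processing, so any site effect on it would come from elsewhere.

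A reader might also fear false positives. For the group comparisons the error runs the other way: blocking with site omitted gives a type I error at or below nominal.

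**Conclusion.** The point holds in a limited form. Site is the randomisation stratum and is not named in any described model. For the powered-versus-passive and group-by-time contrasts, a constant site effect costs nothing, and adding a site main effect gains nothing. For between-participant group comparisons, and for change contrasts where sites differ in change, omitting site makes the test conservative and loses some power. At an assumed 10% to 20% share the loss is about 3 to 7 points for a simple 6-minute walk comparison (78 − 75 and 83 − 76). The correlations and regressions carry site differences of unknown size and direction.

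This rests on an assumed site share and on each participant being measured at one site throughout. It is a minor precision matter to consider, not a threat to validity.

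**What to change.** State that site (three levels, fixed effect) is included as the stratification factor in the mixed models and as a covariate in the penalised and stepwise regressions. Where the group-by-visit contrast is tested, add site-by-visit, at least as a sensitivity analysis, since a site main effect alone cannot help there. Name site beside the other adjusters under Limitations.

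The cost is wording, 2 between-participant degrees of freedom for the main effect, and (3 − 1) × (3 − 1) = 4 more for site-by-visit over three visits. With about 10 participants per site the interaction will be poorly estimated, which is a reason to keep it as a sensitivity analysis.
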